#### Secondary Analyses

We will perform similar 2×2 mixed ANOVAs for each of the following secondary outcomes:

Intrinsic motivation, measured using the interest and enjoyment subscale of the IMICognitive load, using the scale developed by Klepsch et al [29], which includes subscales for intrinsic, extraneous, and germane loadPerceived learning gain, rated on a single-item Likert scale

Each participant completes these measures after each learning task, allowing within-subjects comparisons across modalities and content types.

For all analyses, we will consider both the effect size and the *P* value when interpreting the results. To document test quality, we will report psychometric properties (eg, internal consistency and item characteristics) for both multiple-choice questionnaires. Differences in mean scores are expected due to content difficulty, but reliability (McDonald’s Omega) will be used to ensure comparability across tests.

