**Main effect of complexity (low vs high)**
We anticipate that all residents, regardless of modality, will find the *complex* article more challenging, resulting in lower average test scores compared to the *easy* article, given the higher theoretical density of the former.

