**Modality × complexity interaction**
We hypothesize an interaction such that the effectiveness of the podcast relative to reading will differ by article complexity. Specifically, the performance gap (if any) between listening and reading is expected to be larger for the complex article than for the easy article. In other words, for the easier, case-based article, listening to a summary might achieve nearly the same comprehension as reading, whereas for the complex article, listening to the summary might not capture enough detail, leading to lower comprehension compared to reading the full text.

Additional objectives include evaluating secondary outcomes related to the learning experience: we will compare residents’ intrinsic motivation during the task, subjective cognitive load, and their subjective perception of learning between the 2 modalities. This will provide a more nuanced understanding of how engaging or difficult residents found the learning process in each condition, beyond the factual knowledge gains. Ultimately, the goal is not only to determine which method yields higher test scores, but also to consider which method residents prefer or find more motivating, because an engaging learning experience could encourage more frequent interaction with the scientific literature.

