#### Knowledge Tests

For each article, we developed a multiple-choice questionnaire to assess the comprehension and retention of key information. Each test consists of 10 questions in a single-best-answer format, and the sum of all correct answers represents the knowledge score. The questions cover important points from the article.

All questions were written specifically for this study. We ensured that each question could be answered based on the information in the article and that the AI podcast, if accurate, would also cover those points. We had 2 faculty members with a background in cardiology who were not involved in the study review the questions for content validity and clarity. Internal testing of the final items yielded no problems with comprehensibility.

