#### Primary Analysis

To assess the effect of learning modality and article complexity on comprehension, we will conduct a 2×2 mixed ANOVA with the following factors:

Within-subjects factor: modality (AI-generated podcast vs traditional reading)Within-subjects factor: article complexity (narrative case report vs technical research article)

Each participant completes both a reading task and a podcast task, 1 with the narrative article and the other with the technical article. The assignment of modality to article is counterbalanced. We will test for the main effects of modality and complexity, and their interaction, on knowledge test scores (range 0-10 per article). Effect sizes will be reported using eta squared (η²). Assumptions of normality (Shapiro-Wilk test on residuals) and homogeneity of variance (Levene test) will be examined. If assumption violations are detected, we will consider using robust ANOVA procedures [31].

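### Omega measures reliability within one test and cannot make two unequated tests comparable; near the top of the 0-10 scale, the hypothesised modality-by-complexity interaction may depend on the scale used

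*Protocol article*

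**What the plan says.** Each article has its own purpose-written test (Knowledge Tests): "Each test consists of 10 questions in a single-best-answer format". The outcome is the raw sum, "knowledge test scores (range 0-10 per article" (Primary Analysis). Two outside cardiology faculty members reviewed the items for content validity and clarity. Of the pretest, the article says only this: "Internal testing of the final items yielded no problems with comprehensibility". It gives no item difficulties or score distributions.

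Two of the three hypotheses in Textbox 1 compare results across these two tests. The complexity hypothesis expects the complex article to be harder, "resulting in lower average test scores". The interaction hypothesis states that "the performance gap (if any) between listening and reading is expected to be larger for the complex article than for the easy article".

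Secondary Analyses accepts that mean scores will differ because the content differs in difficulty, and then says reliability "will be used to ensure comparability across tests". It also promises to "report psychometric properties (eg, internal consistency and item characteristics" for both tests as documentation of test quality, but attaches no consequence to what these show.

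**The concern.** Omega asks how consistently the ten items of one test rank the participants who took it. Comparing two tests on a raw 0-10 scale needs something else: items of similar difficulty, or a link between the scales, and similar room to move up and down. Reliability supplies none of these.

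Two hypotheses are affected.

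- **Complexity main effect.** A lower technical mean could reflect a harder article, harder questions or both. Nothing planned separates them.
- **Interaction.** The plan expects higher scores on the easy article and a smaller modality gap there. Compression near the upper bound of the easy test gives that same pattern. A raw-score interaction might then be read as evidence that podcasts fall short specifically for complex papers, when the podcast deficit is the same for both articles on the item-response scale.

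**Working it through.** The article gives no figure for comparability, so there is none to reproduce.

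**Inputs from the article:** 10 items per test, scored 0-10; alpha 0.05; N=60; modality-to-article assignment counterbalanced, taken here as 30 per pairing.

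**Inputs assumed, because the article gives none:** mean reading scores; a podcast deficit of 1 logit on both articles (so no interaction on the logit scale); ability SD 0.8 logit; a guessing floor c of 0, 0.20 or 0.25 (the latter two correspond to 5 or 4 options; the number of options is not stated).

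**Step 1: equal reliability does not mean equal difficulty.** Two 10-item tests were simulated with ability SD 1, equal item difficulty within each test, and intercepts of +2 and -2 logits. KR-20 stood in for omega. Mean scores were 8.44 and 1.55 of 10; KR-20 was 0.573 for both.

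**Step 2: compression for one participant of average ability.** With reading success p, podcast success is

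p' = c + (1-c) × expit(logit((p-c)/(1-c)) - 1), and the raw gap is 10 × (p - p').

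| c | Narrative, p = 0.90 | Technical, p = 0.60 | Raw interaction |
|---|---|---|---|
| 0 | p' = 0.768, gap 1.32 | p' = 0.356, gap 2.44 | 2.44 - 1.32 = 1.12 |
| 0.20 | p' = 0.776, gap 1.24 | p' = 0.415, gap 1.85 | 1.85 - 1.24 = 0.61 |
| 0.25 | p' = 0.779, gap 1.21 | p' = 0.433, gap 1.67 | 1.67 - 1.21 = 0.46 |

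A guessing floor supports the low end of the technical test and roughly halves the artefact.

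**Step 3: the trial's own test.** Write R and L for reading and listening, N and T for the narrative and technical articles. Each participant contributes either RN and LT, or LN and RT. The interaction is (RT - LT) - (RN - LN) = (LN + RT) - (RN + LT), that is, a two-sample comparison of the participants' summed scores between the two pairings. Simulation with 30 per pairing, ability SD 0.8, a 1-logit deficit and difficulties set to give the stated reading means:

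| Reading means N / T | c | Raw interaction (points) | Significant at 0.05 |
|---|---|---|---|
| 9.0 / 6.0 | 0 | 0.97 | about 22% |
| 9.0 / 6.0 | 0.20 | 0.56 | about 12% |
| 9.0 / 6.0 | 0.25 | 0.44 | about 10% |
| 8.5 / 6.0 | 0 | 0.62 | about 11% |
| 8.5 / 6.0 | 0.20-0.25 | 0.27-0.17 | about 5-7% |
| 8.0 / 6.0 | 0.20-0.25 | 0.08-0.00 | about 5% |
| any, no modality effect | any | 0 | about 5% |

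The rates carry simulation error of about one percentage point. If 90% and 60% are set for the average participant instead of as group means, the result without guessing is 0.80 points and about 16%; a guessing floor brings this down to about 9%.

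**Step 4: sensitivity to the other assumptions, without guessing.** At 9.0/6.0, ability SD 0.5 gives 1.05 points and 35%, and SD 1.0 gives 0.92 points and 16%. At 9.5/6.0 the corresponding rates are 74% and 39%. At 7.5/5.5 they are 5-6%.

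**Step 5: what else in the article might cover this.**
- Counterbalancing balances modality across articles, but each test stays tied to its article.
- The robust ANOVA fallback answers non-normality and unequal variance; it does not restore a gap compressed at a bound.
- Limitations concedes that article identity and complexity are confounded, but as a limit on external validity. It does not mention test difficulty or scale compression.

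**The case against.** **The sentence may mean only comparable precision.** It expects means to differ, so it does not claim that omega equalises difficulty. That is fair, and on this reading the remedy for the sentence is a change of wording. But comparability across tests is still more than reliability can deliver, and the sentence offers nothing else.

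**A ceiling cannot create an interaction from nothing.** A reader might infer that a ceiling on the easy test by itself yields a false positive. It does not: with no modality effect the interaction is zero and rejection stays near 5%. A real podcast effect is needed, so the question is how that effect is scaled.

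**The logit scale is not the truth.** The protocol scores its performance gap as number of correct answers. On that scale, losing 2.4 points rather than 1.3 is a genuine interaction. The percentages above are therefore not type I error rates for the protocol's own estimand; they show how often an interaction appears that the item-response scale would not show. For the same reason, requiring significance on both scales would be a debatable extra bar.

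**Easy-test means near 9 are speculative.** This stands. Nothing in the article says where scores will fall. With guessing and lower means the artefact fades, and with guessing and a 1-logit deficit it reverses slightly at 7.5/5.5.

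**Much would be visible anyway.** Means and SDs are reported by modality and article complexity, and item characteristics for both tests. A very easy test also tends to show lower reliability (simulated KR-20 0.44 at a mean of 9.31, against 0.68 at 5.81, ability SD 1.0). A ceiling could thus be noticed afterwards, but the article attaches no consequence to noticing it.

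**Conclusion.** The statement about omega is wrong as written under any assumption: reliability within each test neither links the two tests nor separates item difficulty from article complexity. The complexity main effect is a joint article-and-test difference. The caveat in Limitations covers the choice of articles, not the tests.

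The risk to the interaction is conditional. It needs a real modality effect and easy-test scores of about 9 of 10 or more. With reading means of 9.0 and 6.0, a 1-logit deficit, ability SD 0.8 and 30 per pairing, the raw interaction is about 0.4-1.0 points and significant in about 9-22% of trials, depending on guessing. At easy-test means of 8.5 or lower it is significant in about 5-7% with guessing and up to about 11% without. Apart from N, the test length and alpha, every input is an assumption. The article does not support the inference that a spurious interaction is likely; it shows only that the plan could not recognise a scale-dependent one.

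**What to change.** - Delete the claim that omega ensures comparability; keep omega as a reliability report for each test.
- Pre-specify, as a sensitivity analysis to the raw-score model, an item-level logistic mixed model for correct or incorrect answers, with modality, article, their interaction and period as fixed effects and participant and item as random effects. Add a check that allows a guessing floor, since a plain logistic model ignores it.
- Report the proportion of scores at 9-10 in each modality-by-article cell.
- State in advance that a raw-score interaction not seen on the item-response scale will be reported as scale-dependent.
- Describe the complexity main effect as an article-plus-test difference.

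Cost: some wording and a little more analysis on data the trial will collect anyway. According to Results, no data had been collected at submission (August 2025). No extra participants or items are needed. The downside is a more qualified interaction claim.

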### Ethical Considerations

This study was approved by the Ethics Committee of LMU Munich (23-0688). All procedures were reviewed for compliance with ethical standards in research with human participants.

#### Informed Consent

As noted, we obtain written informed consent from all participants. They are informed that the study is about learning from the medical literature and involves completing tests, but the full details of the interventions are somewhat masked until debriefing to preserve the blinding of the hypothesis. They are told that they can withdraw at any time without penalty.

#### Confidentiality

Each participant is assigned a code; no identifiable personal information is associated with their data. Any publications or reports will present only aggregated results. We do not foresee collecting sensitive personal information; the demographic data collected is minimal.

#### Compensation

As an incentive, all participants will be given the option to enter a lottery to win a €50 (US $58) gift voucher.

## Results

As of the submission of this protocol (August 2025), no participants have been recruited, and no data have been collected. Once data analysis is complete (by early 2026), we will report the trial results according to the CONSORT (Consolidated Standards of Reporting Trials) guidelines, and any deviations from this protocol will be documented and justified. No results are available at the time of publication of this protocol.

## Discussion

### Anticipated Findings

This study evaluates AI-generated audio summaries (*AI podcasts*) as a tool for learning from scientific literature in postgraduate medical education. By directly comparing podcast-based learning with the traditional method of reading full-text articles, we aim to generate evidence on comprehension outcomes, learner motivation, cognitive load, and perceived learning. Because each participant will experience both modalities—reading and listening—our within-subjects design allows for more precise comparisons while controlling for individual differences in prior knowledge, attention, and learning preferences.

The findings will have practical implications for adapting learning materials for resident physicians preparing for board certification. If we find that reading leads to significantly better comprehension than listening, particularly for complex or technical content, this suggests that caution is warranted in using audio summaries as a standalone resource. Resident physicians may miss subtle but clinically important nuances when relying solely on AI-generated podcasts for learning. In such a case, AI-generated audio could still be valuable as a supplementary tool—useful for introducing new material, reinforcing key ideas, or supporting review during time-constrained situations such as commuting or night shifts. The results could also inform developers and content curators about the limitations of current AI summarization models, especially for dense scientific material, and point to areas where greater fidelity and detail are needed.

On the other hand, if comprehension is equivalent across modalities, even for technical articles, this would support the integration of AI-generated audio into formal and informal learning routines. AI podcasts could then be leveraged to increase the flexibility with which physicians access and absorb scientific information, without compromising accuracy or depth. Medical educators and institutions might consider systematically producing and offering AI-generated audio summaries of core readings or recent guideline updates, especially for busy clinicians with limited time for traditional study methods.

Beyond comprehension, our secondary outcomes will help evaluate learner motivation and cognitive engagement. If AI podcasts are associated with higher intrinsic motivation or perceived enjoyment, this could be particularly relevant in postgraduate medical training, where learners face high workloads, cognitive fatigue, and declining study motivation. A more engaging modality could contribute to improved study adherence or knowledge retention over time. Even if comprehension is slightly lower in the podcast format, enhanced motivation might still justify its use—especially as a tool for sustained exposure or re-engagement with difficult topics. Conversely, if resident physicians report lower interest or higher cognitive load when listening, this will provide important feedback for educators and tool developers alike.

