**Conclusions:**

This randomized trial will offer evidence on the effectiveness of AI-generated podcast summaries as a learning tool for medical literature. If listening to an AI-generated podcast yields comprehension comparable to or superior to reading the full article, it could validate an innovative, time-saving approach for busy medical trainees. Conversely, if significant deficits are observed in the podcast group (especially for complex content), the findings will highlight the limitations of AI summaries and the continued importance of traditional reading for thorough understanding.

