Producing high-quality medical education podcasts typically requires expert knowledge, pedagogical insight, technical skills, and significant time for scripting, recording, and postproduction [18]. These constraints limit scalability and personalization, especially for institutions or learners aiming to integrate podcasts into dynamic, content-rich environments, such as medical curricula. Recent advances in generative artificial intelligence (AI) present an opportunity to overcome some of these barriers. AI-powered systems based on large language models can now generate podcast-style summaries of academic content by transforming articles into structured, conversational dialogues [16]. These AI-generated podcasts often simulate discussions between 2 virtual hosts, aiming to translate complex material into an engaging audio narrative. Early research indicates that such podcasts can enhance learner motivation and satisfaction, particularly when personalized according to user needs [19]. Some studies suggest comparable or even superior learning outcomes relative to traditional reading in specific contexts [17,19].

Nevertheless, the educational value of these AI-generated summaries remains largely untested in medical education [18]. AI-generated podcasts may lack the necessary accuracy or lose important contexts, which may cause either worse learning outcomes or potentially even misinform learners and endanger patients. Therefore, this study aims to address these questions through a randomized controlled trial comparing learning outcomes across 2 types of medical articles (practical vs theoretical) in the reading and listening modalities. By examining both knowledge acquisition and learners’ motivational and cognitive responses, we aim to assess whether AI-generated podcasts can serve as a viable tool for engaging residents with scientific literature.

The primary objective of this randomized trial is to compare knowledge acquisition from medical journal articles between 2 learning modalities: listening to an AI-generated podcast versus reading the full text. We seek to determine if one modality leads to superior comprehension in medical residents. A secondary objective is to assess the influence of article complexity on learning outcomes and any interaction between complexity and modality.

In operational terms, the study will test two main hypotheses and one interaction hypothesis, as presented in Textbox 1.

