Study hypothesis.**Main effect of modality (artificial intelligence [AI]**–**generated podcast vs reading the full text)**There may be a difference in knowledge scores between residents who listen to an AI-generated audio summary and those who read the article, regardless of complexity. We will explore the direction of this effect; we expect that reading the full article could confer an advantage for understanding, especially detailed content, but well-crafted audio summaries may yield comparable results for certain types of information.

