#### Sample Size Calculation

We conducted an a priori power analysis using G*Power (version 3.1; Heinrich Heine University) [21] for a mixed ANOVA with 1 within-subjects factor (learning modality: podcast vs reading) and 1 between-subjects factor (article-modality order). To detect a moderate effect size (f=0.25) for the main effects or interactions, with α=0.05 and power (1−β=0.80), the required total sample size is approximately N=44. To account for potential dropouts or missing data, we plan to recruit a total sample of N=60 resident physicians.

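### The article foresees concluding that podcasts are equivalent or comparable to reading, even for technical articles, but its tests and sample size only look for a difference and no margin or interval rule is given

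*Protocol article*

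**What the plan says.** **What is to be tested.** The Introduction gives the primary objective as a superiority question: "We seek to determine if one modality leads to superior comprehension in medical residents". Textbox 1 states the modality hypothesis as undirected: "There may be a difference in knowledge scores between residents who listen to an AI-generated audio summary and those who read the article". The Sample Size Calculation is set up "To detect a moderate effect size (f=0.25) for the main effects or interactions", at α=0.05 and power 0.80, giving about 44 participants with 60 to be recruited. The Primary Analysis states: "We will test for the main effects of modality and complexity, and their interaction, on knowledge test scores". Under Secondary Analyses, interpretation is to weigh effect size together with the P value; no threshold is attached to either.

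**What is to be concluded.** Anticipated Findings sets out two branches. The first is a significant advantage for reading. The second is: "if comprehension is equivalent across modalities, even for technical articles, this would support the integration of AI-generated audio". It adds that this would come at no cost in accuracy or depth. The Conclusions paragraph of the abstract says much the same of a podcast that "yields comprehension comparable to or superior to reading the full article, it could validate an innovative, time-saving approach".

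No section gives an equivalence or non-inferiority margin, an equivalence test or a confidence-interval criterion. The Limitations do not mention that a null result is not evidence of equivalence.

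**The concern.** A test for a difference can show a difference. When it fails to, it has not shown that the two modalities are alike; for that, the interval around the difference must exclude every gap large enough to matter, and someone must first say how large that is. The article names the positive conclusion without saying what result would earn it.

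The stakes are greatest for the technical article. The authors themselves expect the podcast to fall short there (Textbox 1, interaction hypothesis), and the Introduction warns that inaccurate summaries could misinform learners. Anticipated Findings credits the within-subjects design with more precise comparisons. That precision belongs to the overall modality effect. Nobody both reads and hears the technical article, so podcast versus reading on that article compares two different sets of residents.

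**Working it through.** **The plan's own figure.** For a within-subjects effect with m=2 measurements, G*Power uses λ = f²·N·m/(1−ρ). The article does not state ρ. At ρ=0.35, λ = 0.0625·44·2/0.65 = 8.46, and power at N=44 is 0.81; at ρ=0.5 only 34 would be needed. So 44 is attainable, and it is a sample size for detecting a difference. For two means f=0.25 corresponds to d = 2f = 0.5, so 0.5 SD is the gap the plan itself calls moderate.

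**Inputs.** From the article: N=60 recruited, 44 required, complete cases only, one modality per article per person, scores 0–10. Assumed: equal allocation (30 vs 30, or 22 vs 22 if only 44 complete); a common SD σ; ρ between a person's two scores from 0 to 0.5; an illustrative margin of 0.5 SD; σ of 1.5–2.5 points where points are quoted.

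**Technical article alone, in SD units.** SE = √(2/n).
- 30 vs 30: SE = 0.258; 95% half-width = 2.002·0.258 = 0.517.
- 22 vs 22: SE = 0.302; 95% half-width = 2.018·0.302 = 0.608.
- In test points: 0.78–1.29 (30 vs 30) and 0.91–1.52 (22 vs 22) for σ = 1.5–2.5.

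**Chance of missing a true 0.5 SD deficit on that article** (noncentral t, two-sided 0.05).
- 30 vs 30: noncentrality 0.5/0.258 = 1.94; power 0.478; non-significant 52% of the time.
- 22 vs 22: noncentrality 0.5/0.302 = 1.66; power 0.367; non-significant 63% of the time.

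**Two one-sided tests, 0.5 SD margin, true difference 0.** The 90% CI must lie inside ±0.5 SD. Approximately, power = 2Φ(0.5/SE − t₀.₉₅) − 1; the results below also allow for the SD being estimated.

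| Contrast | SE (SD units) | 0.5/SE − t₀.₉₅ | Power |
|---|---|---|---|
| One article, 30 vs 30 | 0.258 | 1.94 − 1.67 = 0.27 | 0.21 |
| One article, 22 vs 22 | 0.302 | 1.66 − 1.68 = −0.02 | 0.05 |
| Overall, N=44, ρ=0 | √(2/44) = 0.213 | 2.35 − 1.68 = 0.66 | 0.49 |
| Overall, N=44, ρ=0.5 | √(1/44) = 0.151 | 3.32 − 1.68 = 1.63 | 0.89 |
| Overall, N=60, ρ=0 | √(2/60) = 0.183 | 2.74 − 1.67 = 1.07 | 0.71 |
| Overall, N=60, ρ=0.5 | √(1/60) = 0.129 | 3.87 − 1.67 = 2.20 | 0.97 |

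The overall rows use SE = √(2(1−ρ)/N), the SE of the mean within-person difference. At 22 vs 22 the expected 90% half-width (1.682·0.302 = 0.507) already exceeds the margin, so the rule is met only when the sample SD happens to be small.

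**Could a null interaction carry the overall result over to the technical article?** The interaction is the difference between the two articles' podcast−reading gaps, with variance 4σ²(1+ρ)/30 at N=60. Its 95% half-width is 2.002·√(4/30) = 0.73 SD at ρ=0 and 2.002·√(6/30) = 0.90 SD at ρ=0.5. It is less precise than the per-article contrast, so a non-significant interaction gives little reassurance.

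**The case against.** The best defence is that equivalence is not an objective. The trial asks about a difference, and the test and sample size fit that question. The disputed sentences are conditional prose in the abstract and Discussion, hedged throughout, and the authors promise to look at effect sizes as well as P values. A fuller protocol or analysis plan, not shown, could say how a null result will be read.

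Much of this stands. The difference tests are valid for the stated objective. A reader might infer that the authors have adopted a rule that P>0.05 means equivalent; no section says so, and the inference rests on the contrast between significantly better and equivalent in Anticipated Findings. A reader might also infer that podcasts are meant to replace reading. The wording there is integration; the abstract's reference to saving time and the Limitations' remark about practical alternatives lean towards substitution but do not state it. Nor does support for podcasts depend wholly on equivalence, since Anticipated Findings says motivation might justify their use even with slightly lower comprehension.

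What does not stand is the effect-size safeguard. A small point estimate inside an interval of ±0.5 SD is compatible with a moderate deficit, and without a threshold it settles nothing. The point is also more than a detail left to another document: the article itself states the conclusion beside an analysis that cannot deliver it.

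**Conclusion.** The concern holds as a mismatch between the foreseen conclusion and the stated analysis. It does not invalidate the planned ANOVA.

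The per-article half-widths in SD units (±0.52 to ±0.61) and the 52–63% chance of missing a 0.5 SD deficit rest only on equal allocation, a common SD and 44 to 60 completers. The equivalence-power figures also depend on the illustrative margin and, for the overall effect, on ρ.

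It would go too far to say that the trial cannot support any equivalence claim. Overall power of 49–97% shows that it might, for a margin as wide as 0.5 SD, although 97% is the most favourable corner of that range. It would also be wrong to call the technical-article contrast the least precise in the trial; the interaction is. What is unsupported is the claim of equivalence even for technical articles, where power is about 21% at best under these assumptions.

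**What to change.** In Anticipated Findings and the abstract's Conclusions, describe a non-significant result as no difference detected. Commit to reporting the podcast−reading difference overall and for each article with 95% CIs, and delete the equivalence claim for technical articles.

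If an overall comparable claim is to be kept, set and justify a margin in test points before data collection; the Results section reports no recruitment at submission in August 2025. Allow the claim only if the 90% CI (two one-sided tests) lies within the margin. Apply the same 90% CI rule to any technical-article claim, and acknowledge that the trial is unlikely to meet it. If a fuller analysis plan already holds such a rule, cite it.

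The margin should be chosen on educational grounds, knowing what N=60 can bear. With σ = 1.5–2.5 points and ρ = 0–0.5, overall power is 0.40–1.00 for a 1-point margin but at most 0.64 for a 0.5-point margin.

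The cost is a few sentences, agreement on a margin if that route is taken, and a more modest stated conclusion. No new data or participants are needed.
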